## 7.0 TREATMENT PLAN/INTERVENTION

Protocol treatment is to begin  $\leq 28$  days of registration.

For questions regarding treatment, please see the study contacts page.

It is acceptable for individual chemotherapy doses to be delivered  $\leq$  a 24-hour (1 business day) window before and after the protocol-defined date for Day 1 of a new cycle. For example, if the treatment due date is a Friday, the window for treatment includes the preceding Thursday through the following Monday. In addition, patients are permitted to have a new cycle of chemotherapy delayed up to 7 days for major life events (e.g., serious illness in a family member, major holiday, vacation that cannot be rescheduled) without this being considered a protocol violation. Documentation to justify this delay should be provided.

Protocol therapy will consist of neoadjuvant chemoradiation followed by neoadjuvant consolidation chemotherapy. Neoadjuvant chemoradiation includes radiation (45Gy + 9 Gy boost) in combination with a fluoropyrimidine (preferred capecitabine; permissible substitution: 5-Fluorouracil continuous infusion).

Subsequently, patients will receive eight cycles of chemotherapy with mFOLFOX6 (may be substituted by 5 cycles of CAPOX) in the control arm or eight cycles of chemotherapy with mFOLFIRINOX in the experimental arm. All patients will undergo assessment 8-12 weeks post-completion of this therapy for the primary endpoint of cCR and based on this assessment recommended further management with watch and wait, repeat assessment 8 weeks later, or surgery

In patients requiring surgery, it may begin any time after assessment for primary endpoint, i.e. 8-12 weeks following completion of chemotherapy.

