**7.1.1 Radiation Therapy Quality Assurance**

Submission of treatment plans in digital format as DICOM RT is required. Digital data must include CT scans, structures, plan, and dose files. This study uses TRIAD for RT data submission. Use of TRIAD requires several preliminary steps (see [Section 6.3](#)). Additional information is available at: <https://triadinstall.acr.org/triadclient/>

Any items on the list below that are not part of the digital submission may be included with the transmission of the digital RT data. <https://irocri.qarc.org/>

Within 3 days of starting radiotherapy, simulation and treatment planning data must be submitted via TRIAD:

- Copies of pre-treatment CT and MRI studies and reports identifying the location of the primary rectal tumor.
- RT treatment plans in DICOMRT format, including treatment planning CT, structures, dose, and plan files.
- RT-1 Dosimetry Summary Form
- Treatment planning system summary report that includes the monitor unit calculations, beam parameters, calculation algorithm, and volume of interest dose statistics.

Within one week of completion of radiotherapy, the following data must be submitted via TRIAD for all patients:

- RT-2 Radiotherapy Total Dose Record Form
- A copy of the patient's radiotherapy record including the prescription and the daily and cumulative doses to all required areas.

Supportive data and forms should be included with the transmission of the digital RT data. Questions regarding the dose calculations or documentation should be directed to:

Protocol Dosimetrist

IROC Rhode Island QA Center

[contact]

Email: <mailto:[contact]>**7.2 Consolidation Neoadjuvant Chemotherapy**

For specific questions or concerns regarding this section, please contact [name] [[contact]](mailto:[contact]) and/or [name] [mailto:[name]\\[contact]](mailto:[contact])

Choice of regimen (mFOLFOX6 for 8 cycles or CAPOX for 5 cycles) for control arm is per the investigator's choice.

Chemotherapy should preferably begin within 2-3 weeks following completion of radiation in patients with mild suggestive as grade 1 or less non- hematological toxicity) or no residual side effects from chemoradiation. In patients with more severe side effects, chemotherapy may be delayed up to 4 weeks at investigators' discretion; further delays must be discussed with the study PI.

Central venous access is strongly recommended.

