## 13.4 Statistical Analysis Plan

### 13.4.1 Analysis Populations:

- **Intent-to-Treat (ITT) Population:** ITT population includes all patients who are properly randomized, regardless of the actual treatment received. The treatment grouping will be according to the original assignment at randomization.
- **Modified Intent-to-Treat (mITT) Population:** mITT population includes all patients who are properly randomized, completed LCRT and started at least one dose of protocol defined chemotherapy treatment. The treatment grouping will be according to the original assignment at randomization.
- **Per-Protocol (PP) Population:** PP population includes all patients who are deemed eligible after randomization, properly randomized, and received at least three cycles of chemotherapy after LCRT. The treatment grouping will be according to the actual treatment received during the first cycle of the chemotherapy.
- **Safety Population:** Safety population includes all patient who received any dose of treatment defined by protocol.

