**13.4.3 Secondary Endpoints:**

The analyses of secondary endpoints will be conducted on mITT and PP population whenever it is applicable and plausible. Safety-related analyses will be performed on the safety population.

The distributions of time-to-event endpoints will be estimated, in each arm, using the method of Kaplan-Meier and compared by a stratified Cox regression model. The binary endpoints will be estimated, in each arm, and compared by chi-squared test or Fisher's exact test. Dose intensity and number of cycles will be summarized by mean, standard deviation, median, Q1, Q3, and range, in each arm, and compared by Wilcoxon Rank Sum test. The maximum grade for each type of adverse events that are possibly, probably, or definitely related to study treatments will be recorded for each patient. The frequency tables will be reviewed to determine the patterns. The overall adverse event rates for grade 3 or higher adverse events will be compared between two treatment groups using Chi-square test (or Fisher's exact test if the data in the contingency table is sparse).

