**13.5 Monitoring****13.5.1 Safety Monitoring****Neoadjuvant treatment completion monitoring:**

To maintain meaningful outcome comparisons between two arms, the completion of neoadjuvant treatment will be monitored. The early off treatment (EOT) rate will be defined as the number of patients who receive fewer than 8 cycles (e.g., 0 to 7 cycles) of neoadjuvant chemotherapy, due to disease progression, death, toxicity, treating physician discretion, and other disease related reasons, after LCRT divided by the number of patients who complete LCRT and start at least one dose of chemotherapy. Patients who withdraw from protocol treatment due to reasons that are not related to disease will be excluded from this analysis.. OPRA trial reported 7% (8/116) of patients who received  $< 8$  cycles of FOLFOX after LCRT in consolidation arm.

We will compare EOT rates between two arms (experimental vs. control arms) when 88 (44 per arm), 174 (87 per arm) and 262 (131 per arm) evaluable patients complete

neoadjuvant chemotherapy or are off neoadjuvant chemotherapy early. Lan-DeMets OF spending function will be used to control multiple comparisons. If the difference in EOT rate (experimental arm minus control arm) is greater than 22.0%, 10.4% and 6.7% (corresponding p-value: < 0.001, 0.016, 0.045) at three time points, respectively, the treatment, toxicity and off treatment reasons data will be thoroughly reviewed and potential protocol modifications, including suggesting halting accrual, will be formulated under the consultations with CTEP. The total sample size of 262 patients will provide 80% power to detect a difference in EOT rate of 10% at a one-sided alpha of 0.05 significance level.

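### The between-arm Wilcoxon test on raw cycle counts mixes regimen choice with treatment delivery, because a full control course can be 5 CAPOX cycles instead of 8

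*Combined protocol and SAP*

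**What the plan says.** Section 13.4.3 covers dose intensity and cycles in one sentence: "Dose intensity and number of cycles will be summarized by mean, standard deviation, median" (followed by quartiles and range), in each arm, and "compared by Wilcoxon Rank Sum test". It neither defines dose intensity nor scales cycles to the planned number, and it does not separate regimens. No significance level or sidedness is given for this test. Secondary analyses use the mITT and per-protocol populations.

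Section 7.0 sets the planned course: "eight cycles of chemotherapy with mFOLFOX6 (may be substituted by 5 cycles of CAPOX) in the control arm", and "eight cycles of chemotherapy with mFOLFIRINOX in the experimental arm". Section 7.2 leaves the "Choice of regimen (mFOLFOX6 for 8 cycles or CAPOX for 5 cycles) for control arm" to the investigator. Tables 7.2.1 to 7.2.3 give 16 weeks for the two 8-cycle regimens and 15 weeks for CAPOX. CAPOX use is not a stratification factor (Section 4.5.1), is not capped, and has no stated expected share.

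Section 1.3 says that the trial will compare treatment compliance between the arms.

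**The concern.** A cycle is not a common unit here. Five CAPOX cycles and eight two-week cycles fill nearly the same calendar time, yet a control patient who completes CAPOX scores 5 and ranks below a triplet patient who stops mFOLFIRINOX after 6 of 8 cycles. CAPOX exists only in the control arm, so the distortion always runs one way: it lowers control counts and makes the triplet look better delivered. In a trial of chemotherapy intensification, delivery of the triplet is one of the first things that readers will want to judge. A prespecified p-value could hide poorer delivery or, with enough CAPOX use, point the wrong way.

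**Working it through.** **Inputs from the documents.** Planned cycles are 8 (mFOLFOX6, mFOLFIRINOX) or 5 (CAPOX). For historical control early stopping, Section 13.5.1 states "OPRA trial reported 7% (8/116) of patients who received" fewer than 8 cycles. The same section plans to detect a 10-point difference, hence 7% versus 17%. Sizes are 148 per arm (phase II) and at most 380 per arm (Section 13.2).

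**Assumptions.** The CAPOX share of the control arm is varied. Early stoppers end uniformly over cycles 1 to planned minus 1. The test is two-sided at 5%.

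**Step 1: reproduce the nearest stated figure.** The plan gives no power for the cycle comparison. For the early-off-treatment comparison it states 80% power with 262 patients and one-sided 5%. With 131 per arm, 7% versus 17% and pooled rate 12%:
- standard error under the null = sqrt(2 × 0.12 × 0.88 / 131) = 0.0402
- standard error under the alternative = sqrt((0.07 × 0.93 + 0.17 × 0.83) / 131) = 0.0397
- z = (0.10 − 1.645 × 0.0402) / 0.0397 = 0.856, so power = 80.4%

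This agrees with the plan, so 7% versus 17% is a fair reading of its own scenario.

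**Step 2: what the Wilcoxon test estimates.** It tests θ = P(triplet count > control count) + ½ P(tie) against 0.5. With 17% versus 7% early stopping:
- against mFOLFOX6 patients: θ = 0.83 × (0.07 + ½ × 0.93) + 0.17 × 0.07 × ½ = 0.450
- against CAPOX patients: 0.83 (triplet at 8) + 2 × 0.0243 (at 6 or 7) + 0.0243 × (0.07 + ½ × 0.93) (at 5) + 0.0243 × 0.14 (at 1 to 4) = 0.895, where 0.0243 = 0.17 / 7

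At CAPOX share s, θ = 0.450 + 0.445s. It passes 0.5 at s = 0.05 / 0.445 = 11%. Below that share the difference is diluted; above it the direction reverses. The timing assumption matters little. If all early stoppers in both arms end at cycle 1, the CAPOX term is 0.83 + 0.17 × ½ × 0.07 = 0.836 and the threshold is 0.05 / 0.386 = 13%. If all end one cycle before completion, the CAPOX term is 1 and the threshold is 0.05 / 0.55 = 9%. With a larger true difference (27% versus 7%, uniform stopping) the threshold is about 23%.

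**Step 3: simulation of the test as written**, 380 per arm, 2,000 trials per row:

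| CAPOX share | 7% vs 7%: triplet significantly higher (false) | 17% vs 7%: triplet significantly lower (correct) | 17% vs 7%: triplet significantly higher (wrong) |
|---|---|---|---|
| 0% | 3.0% | 99.3% | 0% |
| 5% | 59.7% | 58.6% | 0% |
| 10% | 97.6% | 6.6% | 1.1% |
| 15% | 100% | 0.1% | 20.3% |
| 20% | 100% | 0% | 75.2% |
| 30% | 100% | 0% | 100% |

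The nominal rate for the first result column is 2.5%. Repeat runs gave 58 to 61% (false, 5% share), 3 to 7% (correct, 10% share), 17 to 20% (wrong, 15% share) and 73 to 79% (wrong, 20% share).

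With 148 per arm, the false rate at 7% versus 7% is 28% and 68% at shares of 5% and 10%. At 17% versus 7%, correct detection falls from 75% (no CAPOX) to 27% and 5% at those shares, and wrong-direction significance at a 20% share is 37% (35 to 38% over repeats).

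**Step 4: the same trials with cycles received divided by cycles planned.** With equal early stopping, about 5% of trials are significant at every CAPOX share. With 17% versus 7%, lower triplet delivery is detected in 99% (380 per arm) or 75% (148 per arm) and wrong-direction significance is 0%, again at every share.

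**The case against.** The strongest reply is about weight. Number of cycles is not among the secondary endpoints in Section 13.1.2 and feeds no efficacy, futility or stopping rule. That stands: a reader might infer that the cCR or DFS conclusions are at risk, and nothing in the documents supports that.

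The same sentence also plans dose intensity. If defined relative to planned dose, that would be regimen-adjusted. But the plan does not define it, and the cycle count is tested alongside it whatever the definition.

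Section 1.3 does not name cycle count as the compliance measure, and Section 13.5.1 compares early stopping separately. That is fair, though the latter is a monitoring rule at up to 262 patients with its own 8-cycle wording, so it does not replace the final exposure comparison. A finding of more cycles on the triplet would also be literally true; it misleads when read as better delivery.

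The CAPOX share is unknown. A reader might infer that reversal is to be expected, or that the test measures CAPOX use and nothing else. Neither follows. Reversal needs a share above about 11% in the plan's own scenario, and at 5% the test still detects lower triplet delivery in about 58% of trials at 380 per arm. False findings and lost detection, however, already appear at that 5% share.

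A reader might extend the point to the per-protocol rule ("received at least three cycles of chemotherapy after LCRT"), since three cycles is 3/8 = 37.5% of one course and 3/5 = 60% of the other. The effect is negligible. With 20% CAPOX (76 of 380) and 7% stopping early, a quarter of the stoppers end at cycle 2, so a two-cycle minimum would re-admit 76 × 0.07 / 4 = 1.3 patients. At 30% CAPOX (114) and 17% stopping it is 114 × 0.17 / 4 = 4.8. For both primary endpoints this population serves sensitivity analyses only.

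**Conclusion.** The concern holds as a fault in one prespecified exposure analysis. Applied as written, the rank test on raw cycles confounds regimen choice with delivery. At 380 per arm, even a 5% CAPOX share raises the false rate for more cycles on the triplet from a nominal 2.5% to about 60% and cuts correct detection of poorer triplet delivery from about 99% to about 58%. Reversal of direction is conditional: about 1% at a 10% share, about three quarters at 20% and certain in effect at 30%. With almost no CAPOX use the fault is small. These sizes rest on assumed CAPOX shares, uniform stopping times and a two-sided 5% test. Because the analysis uses the mITT and per-protocol populations, 380 per arm is an upper limit. The harm is confined to interpreting treatment delivery between the arms.

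**What to change.** In Section 13.4.3:
- compare between arms the proportion of planned cycles received: cycles given / 8 for mFOLFOX6 and mFOLFIRINOX, cycles given / 5 for CAPOX;
- define dose intensity as delivered dose / planned dose for each drug;
- report raw cycle counts descriptively for mFOLFOX6, CAPOX and mFOLFIRINOX separately, without a between-arm test.

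This changes analysis wording only and no treatment rule. It is best made before exposure data are compared by arm, so that the choice of measure cannot be questioned later. It needs the control regimen, cycles and delivered doses for each patient. The case report forms are not part of these documents, so the team should confirm that all three are recorded.

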disease which would preclude TME. If this rate is high, we will pause the trial to investigate. Also, among patients who start a WW strategy after TNT, then undergo salvage TME, we will monitor the proportion of patients who achieve R0 resection. If this rate is too low, we will pause the trial to investigate data. Additionally, we propose the measurement of ctDNA as an exploratory biomarker and aim to develop a meaningful “minimal residual disease” based risk classification for cCR patients as a potential future tool to help guide patients and clinicians in the difficult shared decision-making process of TME. A well-powered, nationwide trial will help validate the safety and efficacy of organ preservation outside of specialized centers for our patients with rectal cancer; further without a properly powered randomized trial with cCR as the primary endpoint it will be difficult to fully validate the findings of OPRA and make it difficult to formally incorporate a WW approach into standard guidelines for national thought leaders (e.g., NCCN). The trial will compare treatment compliance and AEs between those randomized to the LCRT + mFOLFIRINOX arm to those randomized to the LCRT + mFOLFOX6 arm, and it will identify opportunities for improving delivery of radiotherapy by leveraging the expertise of the NCTN, the Alliance, SWOG, and NRG Oncology.

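### Section 13.4.3 compares unscaled chemotherapy cycle counts between arms, so any control patient given the planned 5 cycles of CAPOX counts as under-treated against the 8-cycle triplet

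*Combined protocol and SAP*

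**What the plan says.** Sections 7.0 and 7.2 set the planned course. The experimental arm receives 8 two-week cycles of mFOLFIRINOX. In the control arm mFOLFOX6 is also 8 two-week cycles, but it "may be substituted by 5 cycles of CAPOX", each lasting three weeks. Section 7.2 leaves this to the site: "Choice of regimen (mFOLFOX6 for 8 cycles or CAPOX for 5 cycles) for control arm is per the" investigator's choice. CAPOX is offered only in the control arm. The documents state no cap on its use, and Section 4.5.1 does not make it a stratification factor.

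Section 13.4.3 takes dose intensity and cycles together: "number of cycles will be summarized by mean, standard deviation, median, Q1, Q3, and range, in each arm, and compared by Wilcoxon Rank Sum" test. It does not scale to planned cycles, convert to weeks or split by control regimen. Dose intensity is not defined. On the analysis sets the section says "The analyses of secondary endpoints will be conducted on mITT and PP population" where applicable.

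Section 1.3 gives the purpose such a comparison would serve: "The trial will compare treatment compliance and AEs between those randomized to the LCRT + mFOLFIRINOX arm" and those randomized to the mFOLFOX6 arm.

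**The concern.** A cycle is three weeks of treatment under CAPOX and two weeks under the other regimens. Counting cycles across arms therefore mixes regimen choice with adherence. Because only controls can receive CAPOX, the error runs one way: it can only make triplet delivery look better.

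For an intensified regimen, deliverability is a result that readers will use. Followed as written, the test can report more cycles on the triplet when patients in both arms complete their planned course equally often. It can also hide a real excess of early stopping on the triplet.

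The per-protocol set does not remove the problem. It requires that a patient "received at least three cycles of chemotherapy after LCRT", so a control who completed CAPOX stays in with the value 5.

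**Working it through.** **Inputs from the documents**
- Planned cycles: 8 for mFOLFIRINOX and mFOLFOX6, 5 for CAPOX (Sections 7.0 and 7.2).
- Patients per arm: 148 (phase II) and 380 (maximum), Section 13.2. The mITT size is not given, so these serve as a bracket.
- Early stopping: 7%, the OPRA figure in Section 13.5.1. The adverse case of 17% v 7% uses that section's 10-point difference.

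**Assumptions**
- The CAPOX share of controls, s, is not in the documents. The range 2-20% is shown, with 0% for reference.
- Early stoppers are spread evenly over 1-7 cycles (1-4 for CAPOX).
- The level is two-sided 0.05, because Section 13.4.3 states none.

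**Check on a stated figure.** Section 13.4.3 gives no power to reproduce. The borrowed rates do reproduce the power in Section 13.5.1: 131 per arm, 7% v 17%, one-sided 0.05 gives 80.4% against the stated 80%.

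**Size of the shift.** The Wilcoxon test responds to θ = P(triplet > control) + ½P(tie), which is 0.5 when there is no difference.

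*Equal stopping, 7% in each arm.* A triplet patient has 8 cycles with probability 0.93 and each of 1-7 with probability 0.01.
- Against an mFOLFOX6 control: 0.5.
- Against a CAPOX completer (5 cycles): 0.93 + 0.02 + ½(0.01) = 0.955.
- Against a CAPOX early stopper (mean 2.5 cycles): 0.93 + 0.045 + 0.005 = 0.98.
- Against CAPOX overall: 0.93 × 0.955 + 0.07 × 0.98 = 0.957.
- So θ = 0.5 + 0.457s, which is 0.523, 0.546 and 0.591 at s = 5%, 10% and 20%.

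*Triplet truly worse, 17% v 7%.* Each of 1-7 cycles on the triplet now has probability 0.17/7 = 0.0243.
- Against mFOLFOX6: ½(0.83 × 0.93) + 0.83 × 0.07 + ½(0.17 × 0.07) = 0.450.
- Against CAPOX: 0.93 × (0.83 + 2 × 0.0243 + 0.0121) + 0.07 × (0.83 + 4.5 × 0.0243 + 0.0121) = 0.895.
- So θ = 0.450 + 0.445s. It reaches 0.5 at s = 0.050/0.445, about 11%. At that share the CAPOX artefact cancels the true deficit.

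**Simulated rejection rates** (Wilcoxon with tie correction, 20,000 trials per cell)

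| CAPOX share | Equal stopping: favours triplet, 148 / 380 per arm | 17% v 7%: finds fewer triplet cycles, 148 / 380 per arm |
|---|---|---|
| 0% | 2.6% / 2.3% | 76.7% / 99.1% |
| 2% | 8.1% / 15.2% | 56.3% / 92.3% |
| 5% | 27.3% / 58.5% | 27.2% / 58.5% |
| 10% | 69.8% / 98.0% | 4.5% / 5.9% |
| 20% | 99.3% / 100% | 0% / 0% |

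In the 17% v 7% case at 20% CAPOX, the test is significant in the wrong direction in 37.5% (148) and 73.8% (380) of trials.

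**Sensitivity at 10% CAPOX**
- Stopping pattern, equal stopping, 148 per arm: the test favours the triplet in 76% of trials if stops come late and in 64% if they come early.
- Per-protocol set, equal stopping: it favours the triplet in 79% (148) and 99% (380).
- Per-protocol set, 17% v 7%: detection is about 1% (148) and under 1% (380), against 63% and 96% with no CAPOX.

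**Percentage of planned cycles instead.** A CAPOX completer now ties with a triplet completer. At every share the test favours the triplet in 2-3% of trials under equal stopping. Under 17% v 7% it detects the deficit in 76-77% (148) and 99% (380).

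**The case against.** The strongest reply is about weight. Number of cycles is not among the secondary endpoints in Section 13.1.2. The comparison has no stated hypothesis, level or decision. Section 1.3 names no measure of compliance, so linking it to this test is an inference. All of that stands, and it limits the point to a reporting matter.

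A second reply is that dose intensity, tested in the same sentence, would show the truth. It could, if defined relative to the planned regimen, but the plan does not define it, and the cycles test would still be reported beside it.

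A third is that the absolute gap is small and the summaries would expose it. At 10% CAPOX under equal stopping, mean cycles are 0.93 × 8 + 0.07 × 4 = 7.72 on the triplet and 0.93 × 5 + 0.07 × 2.5 = 4.825 on CAPOX. The arm difference is therefore 0.10 × (7.72 − 4.825), about 0.3 cycle. Only 0.10 + 0.90 × 0.07 = 16.3% of controls fall below 8, so the median and quartiles would be expected to be 8 in both arms. A careful reader might discount the p-value, but those quartiles would not point to CAPOX as the cause.

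A reader might also infer that the early-off-treatment rule in Section 13.5.1 fails for CAPOX, since it counts the "number of patients who receive fewer than 8 cycles (e.g., 0 to 7 cycles) of neoadjuvant chemotherapy". The documents do not support that. The count is limited to stops "due to disease progression, death, toxicity, treating physician discretion, and other disease related reasons", and the rule separates patients who complete chemotherapy from those who leave it early. Finishing a planned 5-cycle course is completion, and choosing CAPOX is regimen selection. On that reading the rule triggers in about 82% of trials at 17% v 7%, in line with the planned 80%. The probability would fall (to 66%, 41% and 11% at 2%, 5% and 10% CAPOX) only if completers were coded as stopped at physician discretion, which nothing in the text suggests.

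**Conclusion.** The point holds as a minor one. Section 13.4.3 specifies a test that, followed exactly, counts a complete CAPOX course as under-delivery. The direction is certain once any control receives CAPOX; with none there is no bias. The size depends on a share that the documents do not give, and on the assumed stopping rate, stopping pattern and test level. Under those assumptions the distortion is already material at 5% CAPOX, and by 10% a true 10-point excess of early stopping on the triplet goes almost undetected.

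It would be wrong to infer that the trial's conclusions are at risk. Dosing, follow-up, the cCR and DFS analyses, the listed secondary endpoints and the monitoring rules do not use this comparison. What is at stake is a misleading published statement on treatment delivery.

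**What to change.** In Section 13.4.3, compare between arms the percentage of planned cycles received of the regimen started, with 8 as the denominator for mFOLFOX6 and mFOLFIRINOX and 5 for CAPOX. Report raw cycle counts by regimen, descriptively and without a between-arm test.

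This rewords one definition and needs only the regimen started and the cycles received. Sample size, boundaries and look times do not change. Section 13.5.1 needs no change; a sentence stating that patients who complete 5 cycles of CAPOX remain in the denominator as non-events would be an optional clarification.
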